### Research questions and hypothesis

The following questions and hypotheses are being investigated in this study
What effects do the online programs within the three health goals *Losing and Maintaining Weight*, *Increasing Fitness*, and *Smoking Cessation* have on the primary and secondary outcomes variables reported by participants?We assume that we will observe statistically significant improvements with small to medium effect sizes for each program.Will the intervention groups (interactive health programs) in each RCT reveal stronger effects on primary and secondary outcomes in comparison to the control groups (non-interactive health programs)? We will test the hypothesis that the intervention groups’ changes in the primary and secondary outcomes are more positive than the control groups’. Our focus is on long-term effects so we will analyze the change between baseline (t0) and 1 year after the intervention finishes (t3), while short-term effects are part of the secondary analyses. We expect small to medium effect sizes from the comparison between these two groups.Does the intensity of use of health programs have an impact on their effects?The hypothesis we test is that study participants who use their health program more frequently and intensively achieve better outcomes than study participants who use the program less often or less intensively.How satisfied with the programs offered are the study participants in the intervention- and control groups? This question will be examined exploratively in secondary analyses.

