### Specific inclusion criteria for the “Smoking Cessation” RCT

Only people who smoke at baseline (t0) can take part in the “Smoking Cessation” online RCT.

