**Primary**^**i**^**and secondary**^**ii**^**Outcomes**							
Weight	IRES [48]/Changes in mean kilogram	**W**^**i**^,F^**ii**^,S^ii^	1	**x**	**x**	**x**	**x**
Physical activity	Physical Activity and Sport Activity Questionnaire (BSA-F 3.0) [51]/Changes in mean score	W^ii^,**F**^**i**^	17	**x**	**x**	**x**	**x**
Smoking abstinence in the last 30 days	Self –developed/Changes in percentages (dichotomous data)	**S**^**i**^	1	**x**	**x**	**x**	**x**
Health related goal intention	Goal intention [52] [53]; adapted/Differences of mean values	W^ii^,F^**ii**^,S^ii^	1	**x**	**x**	**x**	**x**
Sport- and movement-related self-concordance	Sport- and movement-related self-concordance [54]/Changes in mean score	F^ii^	12	**x**	**x**	**x**	**x**
Self-efficacy (dietary)	Testing phase-specific self-efficacy [55]/Changes in mean score	W^ii^	7	**x**	**x**	**x**	**x**
Self-efficacy (smoking)	Scales for the measurement of self-efficacy and decisional balance in the process of behavioral change in smokers [56]/Changes in mean score	S^ii^	9	**x**	**x**	**x**	**x**
Barrier management in physical exercise	Barriers and barrier management in physical exercise [57]/Changes in mean score	F^ii^	29	**x**	**x**	**x**	**x**
Expectation of consequences	BRAHMS [50]; adapted/Changes in mean score	W^ii^, S^ii^	18	**x**	**x**	**x**	**x**
Action planning	Action plans and coping plans for physical exercise [58]/Changes in means score	F^ii^	13	**x**	**x**	**x**	**x**
Risk perception	Risk perceptions of cigarettes and e-cigarettes [59]; adapted/Changes in mean score	S^ii^	5	**x**			
Perceived goal attainment	Self-developed/Differences in means	W^ii^,F^ii^,S^ii^	2		**x**	**x**	**x**
Eating behavior German Eating Behavior Scale	German Eating Behavior Scale (SEV)*;article submitted [21]/Changes in mean score	W^ii^, F^ii^	32	**x**	**x**	**x**	**x**
Nicotine dependence	Fagerstrom Tolerance Questionnaire *(*FTND [60])/Changes in mean score	S^ii^	6	**x**	**x**	**x**	**x**
Health-related quality of life	Short Form 12 Health Survey (SF-12) [61]/Changes in mean score	W^ii^,F^ii^,S^ii^	12	**x**	**x**	**x**	**x**

Health goals: W=”Losing and Maintaining Weight”; F=”Increasing Fitness”, S=” Smoking Cessation”

Measurement time point: t0 = baseline, t1 = first follow-up; t2 = second follow-up; t3 = third follow-up; IRES = indicators of rehabilitation status

Primary outcome of the related health goals; highlighted in bold

Secondary outcomes of the related health goals

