Possible covariates (see Table 4) will enter the model at level 1 (X) when they are measured at more than one time point or at level 2 (Z) when they are only measured at baseline. The covariates differ in type and number between the three coaches. The components X and Z are therefore only placeholders. The covariates considered may represent real-life conditions of participants existing independently of the program; they can be beneficial or detrimental to participants’ goal attainment or outcomes. The social environment in particular may be conducive or an obstacle [26–30]. The importance of social and emotional support from people, who are close, is also pointed out by the NICE guideline *Behaviour Change: individual approaches* [31]. Tiredness and a decrease in drive and activity are indications of mood disorders. Self-efficacy, motivation and intention to change, as well as functional or physical limitations are predictors for behavioral change and associated with mental health, health status, and comorbidities [32–40]. Furthermore, it is likely that additional addictive behaviors and low degree of mental health will make smoking cessation more difficult [33, 41, 42]. Since past behavior predicts future behavior, as confirmed in a meta-analysis [43], preconditions such as mental health, health status comorbidity, additional addictive behavior, but also social support, assessed at baseline, are considered as program-independent covariates of primary outcomes. We use these covariates, along with sex, age, and primary outcome at baseline to adjust the statistical models in the analyses. In these models, coefficient *γ*_10_ refers to the change over time of the intervention groups (hypothesis 1), while coefficient *γ*_11_ refers to the difference in change between intervention and control group (hypothesis 2).

For the analyses of secondary outcomes, measuring mean changes over time (see Table 3), we use linear mixed models analogous to the primary outcomes in weight loss and fitness. Differences between intervention and control groups in for example “Health related goal intention” or “Perceived goal attainment” will be analyzed using *t* tests.

To test the dose-effect association (hypothesis 3), the outlined model will be adapted—here, we only use the intervention group, so the group variable will be dropped. Instead of the group variable, a variable that code the use (e.g., number of logins) of the coach will enter the model at level 2.

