All metric covariates at level 1 will be group mean-centered, while metric covariates at level 2 will be grand mean-centered. Categorical variables enter as dummy-coded (0/1) variables.

Post-hoc analyses with correction for multiple testing will be conducted to identify changes between specific time points to analyze short-term effects, e.g., between t0 and t1. As effect size, with their 95% confidence intervals, we will calculate Cohen’s *d* bases on the *t* values from the pairwise comparisons from the LMM respective odds ratio for the GLMM.

In the case of the *SmokingCessationCoaching*, we will drop the baseline (T0) from the model, because every case concerns smoking. It is, therefore, not possible to calculate the odds ratio for the change between baseline and post-intervention. Instead, we will use the difference in smoking cessation at post intervention between both groups as the effect size.

Furthermore, we will apply structural equation modeling to test various models for assessing potential mediators of the intervention effect on outcomes.

The analyses are carried out according to the intention-to-treat principle (ITT). In ITT, all randomized participants will be considered in the main analyses. In per-protocol analyses (PP), only those participants will be included who have been randomized, have participated at all time points, and filled out corresponding primary outcomes. The randomization condition for study participants was that they accessed the program at least once.

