### Sample size calculation

#### Randomized controlled trials

We calculated the sample size for each randomized controlled trial (RCT) separately (see Table 5) by considering the effect sizes of the primary outcomes in comparable trials [8–11], the α-error (0.05), and the power we were striving for (1 − *β* = 0.80). Our power analyses were done using GPOWER software. While we assumed a general online-RCT dropout rate of 50% [45, 46], we estimate a dropout rate of about 15% in the medical substudies in light of experiences with similar studies involving personal medical examinations. We have accounted for an additional 10% buffer for the online RCTs.

**Table 5 Tab5:** Sample size calculations for the three RCTs including medical substudies

Health goals	“Increasing Fitness“		“Losing and Maintaining Weight”		“Smoking Cessation“
RCTs	Online questionnaire study	Online-questionnaire study + medical substudy:	Online questionnaire study	Online-questionnaire study + medical substudy:	Online questionnaire study
**Primary outcome**	Physical activity (BSA)	questionnaire study: physical activity (BSA); medical examinations: VO_2 max_	Weight loss	Questionnaire study + medical examinations: weight loss	Abstinence from smoking
**Effect assumption for primary outcome**	effect size = 0.25	questionnaire study: effect size = 0.25 ; medical examinations: effect size = 0.45	Effect size = 0.50	Effect size = 0.50	15% in intervention group versus 2% in control group
**Required case-number results** (two-sided, alpha = 0.05, beta = 0.80)	253 (for each intervention group IG and control group CG)^1^	79 (for each IG and CG)^2^	253 (for each IG and CG)^1,3^	64 (for each IG and CG)^2^	77 (for each IG and CG)
**(assumed dropout)** **minimally required sample size**	(50%) 506 (for each IG and CG)	(15%) 93 (for each IG and CG)	(50%) 506 (for each IG and CG)	(15%) 75 (for each IG and CG)	(50%) 154 (for each IG and CG)
**total sample size (IG + CG + ca. 10% buffer for questionnaire study**	(506 + 506) × 1.1 *N* = 1.114	(93 + 93) *N* = 186	(506 + 506) × 1.1 *N* = 1.114	(75 + 75) *N* = 150	(154 + 154) × 1.1 *N* = 339

IG = intervention group (specific online coach for the health goal chosen), CG = control group (specific health information for the health goal chosen)

^1^As we aimed to assess the groups undergoing additional medical exams separately from those only completing the online questionnaire, the former group’s sample size is not included in this calculation

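### Smoking RCT: with baseline dropped, the coefficient assigned to hypothesis 2 compares only t1–t3 trends, and no between-arm test of abstinence at t3 is named

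*Protocol article*

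**What the plan says.** All references are to the Protocol article.

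- **Research questions and hypothesis.** For the comparison of arms (hypothesis 2): "Our focus is on long-term effects so we will analyze the change between baseline (t0) and 1 year after the intervention finishes (t3". The same sentence adds that "short-term effects are part of the secondary analyses".
- **Table 3 and inclusion criteria.** The primary outcome of the smoking RCT is "Smoking abstinence in the last 30 days", a yes/no item asked at t0 to t3. "Only people who smoke at baseline (t0) can take part", so abstinence at t0 is 0% in both arms by design.
- **Summative evaluation, model.** One basic model serves all three primary outcomes: intercept, group, one time variable coded 0 to 3, and group by time, with random intercepts and slopes. The coefficient γ11 "refers to the difference in change between intervention and control group (hypothesis 2").
- **Summative evaluation, smoking.** "we will drop the baseline (T0) from the model, because every case concerns smoking". Because an odds ratio for change from baseline cannot then be calculated, "we will use the difference in smoking cessation at post intervention between both groups as the effect size". Hypothesis 2 is not reassigned, time is not recoded, and no contrast at t3 is named. The pairwise comparisons described just before are post hoc and aimed at short-term effects.
- **Sample size calculation, Table 5.** The smoking RCT is sized on "15% in intervention group versus 2% in control group", with 77 evaluable per arm, 154 per arm after 50% dropout, and 339 in total with the buffer. The time point of the two rates is not given.

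**The concern.** In the weight and fitness RCTs t0 stays in the model. Both arms start from a common level, so group by time carries the treatment effect on change from baseline. In the smoking RCT that anchor is removed. Any advantage already present at t1 moves into the level difference between arms, and γ11 keeps only what happens to that advantage afterwards, through relapse and late quitting alike.

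The coefficient named for hypothesis 2 therefore no longer answers the long-term question, and the replacement effect size is tied to an undefined time point. Three quantities remain available: a t1 difference, a t1–t3 slope difference and a t3 difference. They can disagree, and the article does not say which decides the primary question. That leaves room to choose once the results are known.

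**Working it through.** **1. What γ11 is without t0.** The model's log odds ratio (intervention versus control) at time t is

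log OR(t) = γ01 + γ11 · t

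Over t1 to t3, two steps apart, γ11 = [log OR(t3) − log OR(t1)] / 2 when the trend is linear. The between-arm effect at t3 is γ01 + 3·γ11 if time stays coded 1–3, or γ01 + 2·γ11 if recoded 0–2. The article states no recoding. With codes 1–3, γ01 alone is an extrapolation back to the omitted baseline.

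**2. Reproducing the plan's own figure.** Inputs from Table 5: 15% versus 2%, two-sided α 0.05, target power 0.80, equal allocation. Exact power of Fisher's test is

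power(n) = Σa Σb Bin(a; n, 0.15) · Bin(b; n, 0.02) · 1{Fisher p ≤ 0.05}

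- n = 76 per arm: 0.7935
- n = 77 per arm: 0.8010

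So 77 reproduces exactly. Other formulas do not give it: pooled normal 72, with continuity correction 86, unpooled 69, arcsine 60. Inflation: 77 / (1 − 0.50) = 154; (154 + 154) × 1.1 = 338.8, i.e. 339. The trial was sized on one comparison of two proportions at one time point.

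**3. γ11 under the planning rates.** Suppose 15% versus 2% holds at t1, t2 and t3 (an assumption). At each time

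log OR = ln(0.15/0.85) − ln(0.02/0.98) = −1.73 + 3.89 = 2.16

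γ11 = (2.16 − 2.16) / 2 = 0. A benefit of the full planned size gives a true interaction of zero.

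**4. γ11 when the odds ratio shrinks.** Take an illustrative 30/20/15% versus a flat 2%:

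- t1: (0.30/0.70) / (0.02/0.98) = 21.0, log 3.04
- t2: (0.20/0.80) / (0.02/0.98) = 12.25, log 2.51
- t3: (0.15/0.85) / (0.02/0.98) = 8.65, log 2.16

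γ11 ≈ (2.16 − 3.04) / 2 = −0.44 per step. The sign favours control although the planned t3 difference is fully present.

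**5. Illustrative simulation.** The article gives neither the trajectories nor the within-person correlation, so both are assumed. A logistic GEE with robust standard errors stands in for the GLMM. The table uses a logit random intercept with SD 3 and 600 runs; the t1 and t3 contrasts are uncorrected z-tests. Entries are rejection rates at 77 / 154 per arm.

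| Assumed abstinence, t1/t2/t3 | log OR, t1/t2/t3 | γ11 test | t1 contrast | t3 contrast |
|---|---|---|---|---|
| 15/15/15% vs 2/2/2% | 2.16/2.16/2.16 | 0.10 / 0.05 | 0.88 / 0.99 | 0.89 / 0.995 |
| 30/21/15% vs 4.65/3/2% | 2.17/2.15/2.16 | 0.10 / 0.07 | 0.998 / 1.00 | 0.91 / 0.998 |
| 25/15/8% vs 8/8/8% | 1.34/0.71/0 | 0.64 / 0.89 | 0.85 / 0.98 | 0.04 / 0.05 |
| 28/21/15% vs 15/8/2% | 0.79/1.12/2.16 | 0.42 / 0.73 | 0.51 / 0.79 | 0.88 / 0.99 |

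In row 3 the interaction is adverse to the intervention while the t1 contrast favours it, and there is no difference at t3.

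With a latent correlation of 0.8 instead, constant 15% versus 2% gave γ11 rejection of about 12–14% at 77 per arm and 5–7% at 154. Under the trajectory in step 4, γ11 was significantly negative in about 31–35% of trials, while Fisher's test at t3 had 80–99% power. Rates above 5% under a zero interaction reflect sparse events in a 2% control arm.

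**The case against.** The strongest case on the other side has four parts.

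*The smoking paragraph may already replace the test.* It recognises that change from baseline cannot be modelled and substitutes a between-arm difference, with confidence intervals for effect sizes promised just before. So a reader should not infer that the arms are never compared directly. What stands against the plan is that this is called an effect size, not the test of hypothesis 2, and γ11 is never withdrawn.

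*Post intervention may mean t3.* A reader might infer that the effect size is fixed at week 6. The documents do not settle this: no assessment carries that label, and without t0 every remaining one follows the program. Program end is the natural reading, because t3 is described as one year after the intervention finishes. If t3 was meant, this half of the point reduces to an undefined term, but γ11 is still not a t3 test.

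*The same GLMM yields a t3 contrast, and the detail may sit in the analysis plan.* The first part is true, and data, outcome and model class are sound. But this is more than an omission: the article states which coefficient tests which hypothesis, then changes the model so that the statement fails for smoking.

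*The wrong-way result depends on the scenario.* It does. A fading benefit makes γ11 negative only if the odds ratio shrinks. In row 2 of the table the risk difference falls from about 25 to 13 points with no signal in γ11, and in row 4 the odds ratio grows and γ11 favours the intervention.

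A reader might also infer that hypothesis 1 goes untested for smoking. That is weak: baseline abstinence is 0% by design, so each follow-up proportion is itself the change, and Table 3 lists changes in percentages.

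**Conclusion.** The point holds for the smoking RCT only; weight and fitness keep t0. As written, hypothesis 2 is assigned to a coefficient that, without t0, measures the between-arm difference in log-odds trend from t1 to t3. That it is zero under a constant odds ratio and negative under a shrinking one is algebra and needs no simulation. No between-arm test at t3 is named, although t3 is the declared focus, and the effect size refers to an undefined time.

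On size: under constant 15% versus 2%, γ11 rejects in about 5–14% of simulated trials, essentially its type I error. The single-time-point test on which the trial was sized has 80.1% power at 77 per arm. The simulated rates are illustrative. They rest on assumed trajectories, an assumed correlation and a GEE stand-in for a GLMM with random slopes, and the 154-per-arm figures assume no dropout.

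The sample size is not in dispute; 77, 154 and 339 all reproduce. Because this is the primary analysis of one of the three trials, the wording should be settled before outcome data are analysed.

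**What to change.** For the smoking RCT:

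- Name the between-arm contrast in 30-day abstinence at t3 as the test of hypothesis 2, reported as an odds ratio and a risk difference with 95% confidence intervals. Take it from a logistic model at t3, or from a t1–t3 model with time as a categorical factor and the group contrast evaluated at t3.
- State that γ11 is not the test of hypothesis 2 in this trial. If it is kept, describe it as the difference in trend after program end.
- Define post intervention by its assessment label, and make the t1 and t2 contrasts secondary, in line with the stated focus.

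The cost is a change of analysis wording. No new data are needed, and the planned 77 evaluable per arm already fits a t3 contrast of 15% versus 2%, provided those rates are meant for t3.

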#### Sensitivity analysis and missing values

We will compare the results from intention-to-treat (ITT) analyses with per-protocol analyses (PP) and drop-out analyses. We test if participants, who have continuously taken part in the online survey, achieve better outcomes. Due to different procedures to impute missing values (see below), we will use linear mixed models, (a) with imputed covariates on ITT and PP analyses and (b) without covariates in ITT and PP analyses to compare the raw change in outcomes over time.

In addition, we will consider data on program use, (a) between intervention- and control-groups and (b) within intervention groups, between participants who use the program only once and those who use it multiple times.

In the missing value analysis, we analyze the patterns of missing values as well as frequency for cases and variables. The missing values will be imputed using multiple imputation (MI) technique, if the assumption of missing at random (MAR) or missing complete at random (MCAR) holds.

The imputation approach differs between ITT and PP because in PP, we only include participants without missing values on outcome criteria in the analysis. Therefore, only missing values on predictor variables will be imputed, but not for the outcome variables, while in the ITT analysis, predictor variables as outcome variables will be imputed too.

#### Formative evaluation

Our fourth and final investigative aim is to characterize the intervention- and control-group participants’ ways of use and satisfaction with their corresponding online program as further secondary outcomes. To that end, the first step will be to conduct a descriptive analysis; in step 2, we will test via regression models our hypotheses regarding predictors of satisfaction.

The telephone interviews with users of the *SmokingCessationCoach* (intervention group of the corresponding RCT) will be analyzed taking a qualitative content analysis approach. The transcripts of the interviews will be coded and analyzed according to a deductive and inductive approach. We will form main- and subcategories out of the identified themes. Deductive main categories will correspond to the main topics of the interview guideline. Inductive categories will result from additional content mentioned by the participants in the interviews. Subcategories will form subordinate topics or different ratings of a main category. According to the categorization system, transcripts will be coded, ordered, summarized and systematically interpreted [44]. For illustration purposes, the presentation of the results will include individual quotes of the participants.

### Sample size calculation

#### Randomized controlled trials

We calculated the sample size for each randomized controlled trial (RCT) separately (see Table 5) by considering the effect sizes of the primary outcomes in comparable trials [8–11], the α-error (0.05), and the power we were striving for (1 − *β* = 0.80). Our power analyses were done using GPOWER software. While we assumed a general online-RCT dropout rate of 50% [45, 46], we estimate a dropout rate of about 15% in the medical substudies in light of experiences with similar studies involving personal medical examinations. We have accounted for an additional 10% buffer for the online RCTs.

**Table 5 Tab5:** Sample size calculations for the three RCTs including medical substudies

Health goals	“Increasing Fitness“		“Losing and Maintaining Weight”		“Smoking Cessation“
RCTs	Online questionnaire study	Online-questionnaire study + medical substudy:	Online questionnaire study	Online-questionnaire study + medical substudy:	Online questionnaire study
**Primary outcome**	Physical activity (BSA)	questionnaire study: physical activity (BSA); medical examinations: VO_2 max_	Weight loss	Questionnaire study + medical examinations: weight loss	Abstinence from smoking
**Effect assumption for primary outcome**	effect size = 0.25	questionnaire study: effect size = 0.25 ; medical examinations: effect size = 0.45	Effect size = 0.50	Effect size = 0.50	15% in intervention group versus 2% in control group
**Required case-number results** (two-sided, alpha = 0.05, beta = 0.80)	253 (for each intervention group IG and control group CG)^1^	79 (for each IG and CG)^2^	253 (for each IG and CG)^1,3^	64 (for each IG and CG)^2^	77 (for each IG and CG)
**(assumed dropout)** **minimally required sample size**	(50%) 506 (for each IG and CG)	(15%) 93 (for each IG and CG)	(50%) 506 (for each IG and CG)	(15%) 75 (for each IG and CG)	(50%) 154 (for each IG and CG)
**total sample size (IG + CG + ca. 10% buffer for questionnaire study**	(506 + 506) × 1.1 *N* = 1.114	(93 + 93) *N* = 186	(506 + 506) × 1.1 *N* = 1.114	(75 + 75) *N* = 150	(154 + 154) × 1.1 *N* = 339

IG = intervention group (specific online coach for the health goal chosen), CG = control group (specific health information for the health goal chosen)

^1^As we aimed to assess the groups undergoing additional medical exams separately from those only completing the online questionnaire, the former group’s sample size is not included in this calculation

^2^As the questionnaire study’s outcomes are secondary for this group, our required sample size refers to the medical exam’s outcome

^3^As physical activity is a key secondary outcome for the Lose Weight group, we have considered both primary and secondary outcomes (physical activity) in determining the required sample size

